**Primary Outcome**				
**· Barthel-Index**	+	+		+
**Secondary Outcomes**				
**· Delirium (DOS)**	+			
**· Cognition (MMSE)**	+			+
**· Mobility (SPPB)**	+			+
**· Falling concerns (FES-I)**	+			+
**· Frailty**	+			+
**· Weight, height, BMI**	+			+
**· PAC capability**	+	+		
**· Quality of life**	+	+		+
**· Informal network**				+

Ninety days after PAC discharge, telephone contact will be established with the older person to ask whether they want to continue participating in the study and to verify their address.

As part of the process evaluation, the primary relatives (*n* = 30) will be individually interviewed 6 months after PAC discharge using constructive grounded theory to identify impacts of the PAC programme on their quality of life during their daily routines [56]. These interviews will be conducted by trained PZZ staff members not involved in the PAC programme.

The timepoints are labelled T0 to T3. The plus symbol (“+”) indicates the timepoints at which each instrument will be applied. At T2, no outcomes will be evaluated, but the participants’ residence and continued participation will be verified.

### Statistical analysis

Data analysis will be performed using R-Project software version 3.5.2. The socio-demographic data will be analysed descriptively (frequencies, central tendencies, standard deviations). For the primary endpoint, the BI, we will estimate unadjusted cumulative odds using the basic model presented in the sample size section to detect BI changes between baseline and follow-up measures. The model will further be adjusted for age, sex, and secondary endpoints mobility and frailty, which have been identified as driving factors leading to institutionalisation in a nursing home. Both unadjusted and adjusted OR with corresponding 95% confidence intervals will be reported. Similarly, unadjusted and adjusted generalised linear mixed-effects models of the appropriate family and link function will be used to estimate the parameters of the secondary endpoints. Statistical significance will be established at *p* < 0.05.

### Analysis of interviews

Process evaluation analysis of the informal caregiver networks will apply constructive grounded theory [56], run through the Atlas.ti® software Version 8.4.4. Within constructive grounded theory, data analysis and data collection take place simultaneously, which is why data analysis will begin with the first interviews. Sample size depends on theoretical saturation. This leading criterion for the grounded theory method can vary [56]. In this case, we assume that we will interview up to 30 relatives. Using comparative strategies (so-called “constant comparisons”), text passages, events, strategies and persons will be compared to identify content similarities and differences. Further analysis will be conducted by employing two analytical steps: initial and focused coding. A data segment will be coded row by row during initial coding to develop categories. In the next step (focused coding), the properties and connections of the codes will be developed so that an explanatory model of daily routines after the PAC programme is created in an inductive process. The process will be documented using memos to ensure the credibility and quality of the analysis [56].

## Discussion

The complexity of older people’s treatment requirements and the lack of information about the sustainability of PAC in Switzerland highlight the urgent need for an evaluation of PAC. Current data do not permit any further differentiation of geriatric rehabilitation programmes and, more specifically, of PAC treatment programmes for people with injuries, musculoskeletal diseases and circulatory diseases [31–33]. Older people are often multimorbid. In Swiss university hospitals, 79% of patients (median age: 68 years old) are multimorbid and have seven types of illnesses (median), four of which are chronic (median): chronic heart disease, chronic kidney disease, solid malignancy and substance-related disorders. Each of these four types of illness comprises two to eight comorbidities. The most common are neurological diseases, heart/kidney diseases, malignancy, miscellaneous diseases and psychiatric diseases [57]. Therefore, this study aims to evaluate functional status using the BI as the primary endpoint. In addition, quality of life and the informal network (relatives) will be assessed as secondary endpoints.

Nevertheless, there are some points to discuss. First, a programme of 6 weeks for multimorbid patients is often too short to gain independence and depends on the severity of the impairments. Second, improved functions are not always clinically significant. There may be a difference between performing in a laboratory setting and coping with daily life. An effective program always takes place in interaction with the environment [58]. Third, for people with neurological diseases, for example, dealing emotionally with role changes due to physical limitations or reduced social participation is essential for living as independently as possible at home [59, 60].

PAC programmes include repeated assessments, individual treatment and therapy plans (e.g. physiotherapy, occupational therapy and nursing). The therapies take place individually and in groups. In assessment interviews, older people and their family members are informed about their status, treatment progress and plan. Discharge planning is also important. Older people in PAC receive information and documents on continuing care, medications, therapies and aids as needed. Their general practitioners are also informed so that further medical care is ensured.

If the results of this study show that PAC programmes delivered in nursing homes improve the participants’ functional status to the point that they can return home, then the tested programmes could be considered an effective way to delay the elderly from permanently residing in a nursing home. Furthermore, having evidence of a successful PAC programme will offer specialised nursing homes the opportunity to differentiate their services and transform their image from the “last station in life”. Having access to a comprehensive geriatric assessment tool will also enable PAC staff to develop treatment plans, which decreases the probability that older people will be institutionalised [7, 9].

According to the British Medical Research Framework for complex interventions [61], this study is categorised as a pilot study to determine whether the PAC programme can improve older people’s functional status, as measured using the BI. Moreover, the repeated measures study design allows the assessment of functionality over several months and ensures that the intervention’s short-term and long-term effects can be adequately captured and differentiated [62].

In sum, we will determine the sustainability of the PAC programme from the perspectives of the elderly and their relatives over 6 months. We expect that the PAC programme will improve the functional status of older people and reduce the burden on their relatives.

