### Aims and hypothesis

The aim of this study is to evaluate the sustainability of PAC using functionality as the primary endpoint, measured using the BI. We hypothesise that the PAC programme improves a patient’s functional status (measured using the BI) to a level that allows them to return home after completing PAC in the nursing home and maintain a moderate increase in BI for at least 6 months after discharge (odds ratio = 1.5). Based on the study’s exploratory nature, we assume that moderate improvements are associated with a substantial gain in independence.

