## Methods

The SPICE framework is used to describe the study components [36]. The version adapted for this study contains the following elements: S = study design, setting, sample size, P = participants, I = intervention/issue of interest, E = Endpoints, including their specific analyses. Comparison (C) has been omitted, as this is not a clinical trial.

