### Study design and setting

The Prevention Admission into Nursing homes (PAN) study is a three-site, multicentre, exploratory, prospective, longitudinal pilot study in Swiss nursing homes without a control group. All centres (*n* = 3) are located in Zurich and the study will examine older people (*n* = 260) enrolled in PAC treatment. Additionally, a qualitative process evaluation will assess relatives’ perspectives (*n* = 30).

This study will be led by Zurich University of Applied Science’s health department and the department of Nursing Homes of the City of Zurich (PZZ) and will last approximately 24 months.

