### Endpoints

The following outcomes will guide the evaluation of the PAC programme.Functional status as the primary endpoint

Functional status will be measured with the BI [38] at PAC entry (T0), PAC exit (T1) and 6 months after PAC discharge to the home environment (T3). The BI is a ten-item scale with either 0, 5, 10 or 15 points allocated for each item (maximum total score of 100 points = maximum functional status). The BI is a validated and common instrument used to assess functionality in rehabilitation care [38, 39]. For use with older and multi-diagnosed people, there might be imprecision when testing takes place by different observers [40]. To the best of our knowledge, little is known about the sensitivity to changes in the BI [41]. A clinically meaningful change is to be determined by the patients themselves. Recommended BI cut-off points to determine overall independence are problematic. Overall, a five-point difference can have completely different meanings for individual daily life independence. Collin and colleagues [39, 41] recommended that a 20-point change be considered as clinically significant. For the individual use of BI, other endpoints must also be considered.

All items will be collected through direct observation by study personnel or interviews with those affected, their relatives or the nursing staff.2.Independence as the secondary endpoint

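### BI change in an uncontrolled cohort cannot show return home or delayed nursing-home residence, and residence is not an analysed endpoint

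*Protocol article*

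**What the plan says.** The protocol article describes an "exploratory, prospective, longitudinal pilot study in Swiss nursing homes without a control group". Its Methods section adds: "Comparison (C) has been omitted, as this is not a clinical trial".

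Aims and hypothesis expects the programme to raise function "to a level that allows them to return home after completing PAC in the nursing home", with a moderate BI gain kept for at least 6 months. The primary endpoint is set out under Endpoints: "Functional status will be measured with the BI [38] at PAC entry (T0), PAC exit (T1) and 6 months after PAC discharge to the home". The last of these time points is T3. Sample size defines δ2 as the change in BI from PAC entry to 6 months, tested with H0: δ2 ≤ 0.4 against H1: δ2 > 0.4.

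The secondary endpoints and Table 1 cover delirium, cognition, mobility, falling concerns, frailty, weight/height/BMI, PAC capability, quality of life and informal network. The notes under Table 1 say that no outcome is evaluated at T2, but that participants' "residence and continued participation will be verified". Statistical analysis contains no analysis of residence.

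The Discussion draws this inference: "then the tested programmes could be considered an effective way to delay the elderly from permanently residing in a nursing home". The condition it attaches is that the results show the programmes to "improve the participants’ functional status to the point that they can return home".

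**The concern.** To call a programme effective in delaying permanent residence is a comparative statement about when, or whether, people move into a nursing home. It needs that outcome and some comparison with what would have happened otherwise. The plan has neither as an analysed element. The first half of the hypothesis, function good enough to go home, has no measure either: there is no BI threshold and no return-home endpoint.

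The study's own name refers to preventing nursing-home admission, so readers are likely to take a favourable BI result as evidence of that. If the Discussion wording is carried into the report, a before-after gain could be read as a programme effect on institutionalisation.

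**Working it through.** **1. Does the plan measure the outcome in the conclusion?**

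| Element | What the article provides |
|---|---|
| Return home after PAC (Aims and hypothesis) | No endpoint for discharge destination at T1 |
| Permanent nursing-home residence (Discussion) | No endpoint for residence or admission; residence verified at T2 only, not as an outcome |
| Closest secondary endpoint | Informal network at T3, which counts use of caregivers, not where the person lives |
| Analysis | Models for BI and the listed secondary endpoints only |

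**2. Can the BI stand in for it?** The article argues against this itself. The Background says better function is no assurance of going home. Endpoints calls BI cut-offs for independence problematic, and none is fixed. So a BI result cannot show that the condition in the Discussion sentence has been met.

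**3. Can δ2 be credited to PAC?** Write δ2 = p + r, where p is the programme effect and r is the change that would occur without PAC. Every participant receives PAC, so only the sum is estimable. Participants arrive after an acute hospital stay (Intervention), have PAC potential of at least 3 (Participants) and are expected to go home within 8 weeks (Abstract). Some r > 0 is plausible, but the article gives no recovery data, so its size is unknown. A larger sample would estimate p + r more precisely without separating the two parts.

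**4. What r would it take to reject H0 with p = 0?** The threshold of 0.4 logits corresponds to OR = exp(0.4) = 1.49, matching the stated value of about 1.5. A gain of exactly 0.4 lies inside H0. A simulation of the cumulative-logit random-intercept model (n = 200, ICC 0.2, true δ1 = δ2 = 0.4, 5 or 8 equally likely categories, 200 runs each) rejected H0 in the upper tail of a two-sided 5% test in 1.5% and 3.5% of runs; the nominal rate is 2.5%. The standard error was about 0.18, so a 50% chance of rejection needs roughly 0.4 + 1.96 × 0.18 = 0.75 logits. The categories, cut-points and δ1 are assumptions, because the article does not give them.

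**5. How precise would a residence proportion be?** The plan's n is 200 × 1.30 = 260 (Sample size); whether that is the right allowance for dropout is a separate matter. With 30% loss, 260 × 0.70 = 182 remain. The half-width is 1.96 × √(q(1 − q)/n), where q is the assumed proportion at home; the article gives no value for q.

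| q | n = 260 | n = 182 |
|---|---|---|
| 0.50 | 1.96 × √(0.25/260) = 6.1 points | 1.96 × √(0.25/182) = 7.3 points |
| 0.70 | 1.96 × √(0.21/260) = 5.6 points | 1.96 × √(0.21/182) = 6.7 points |
| 0.90 | 1.96 × √(0.09/260) = 3.6 points | 1.96 × √(0.09/182) = 4.4 points |

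**The case against.** The missing comparator is a disclosed choice in a study labelled exploratory and pilot. The sentence at issue is conditional, hedged Discussion text, and the test, sample size and primary analysis do not depend on it. The Discussion also cautions that functional gains are not always clinically significant, and Endpoints says other endpoints must be considered when the BI is used individually.

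Most of this stands, and it rules out three stronger readings that a reader might infer:

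- *That the study is committed to declaring PAC effective against institutionalisation once δ2 is positive.* No such decision rule exists. The stated condition is function sufficient for return home, not rejection of H0.
- *That a spontaneous gain of 0.4 logits would produce a positive result by itself.* It would not, because 0.4 belongs to the null hypothesis. Only a gain clearly above it would often be declared positive.
- *That residence goes unseen.* It is verified at T2, and T3 is described as a measurement in the home environment. The defect is that residence is not a defined, analysed endpoint.

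The objection does not rescue the inference. A hedged claim of effectiveness still needs an outcome and a comparison, and the exploratory label argues for a more modest conclusion. Nor is this a detail lost in condensing the protocol: the article gives a full endpoint list and schedule, and states outright that there is no control group.

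**Conclusion.** The point holds as a mismatch between the suggested interpretation and the design. What the study can report is change in BI over time in an uncontrolled cohort selected for likely return home. It cannot attribute that change to PAC, and BI change alone cannot establish return home or delayed institutionalisation.

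The share of δ2 due to recovery without PAC cannot be sized from the article. That such recovery exists is a clinical expectation, not a documented figure. The missing comparator alone defeats attribution, whatever the size of r. The planned test and sample size are untouched by this point; what needs changing is one endpoint and the wording of the conclusion.

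**What to change.** 1. Add place of residence (home, nursing home, hospital, dead) at T1, T2 and T3 as a descriptive secondary endpoint. Report it for all enrolled participants with 95% confidence intervals, and show unknown status as its own category. This gives the return-home part of the hypothesis a direct measure.
2. Reword the Discussion so that the study reports change in function and the proportion living at home in an uncontrolled cohort, with no effect on institutionalisation attributed to PAC. Leave effectiveness claims to a later controlled study. The new endpoint alone would not justify a claim of delay.

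Cost: modest. Destination at T1 should be available from discharge planning, T2 residence is already verified, and T3 contact is planned. The extra work lies in ascertaining residence and vital status for people who withdraw or die, within what their consent allows. The other cost is a more modest conclusion.

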## Data Availability

The datasets produced as part of the study are available on request from the corresponding author.

## Abbreviations

BI: Barthel Index
BMI: Body Mass Index
DOS: Delirium Observation Scale
FES-I: Falls Efficacy Scale-International
MMSE: Mini-Mental State Examination
PAN: Prevention Admission into Nursing homes
PAC: Post-acute Care
PI: Principal Investigator
SPPB: Short Physical Performance Battery
RAI_NH: Resident Assessment Instrument for Nursing Homes
